## Abstract

**Background:**

Hypalbuminemia is associated with numerous postoperative complications, so a perioperative albumin substitution is often considered. The objective of SuperAdd is to investigate whether substitution of human albumin, aiming to maintain a serum concentration > 30 g/l, can reduce postoperative complications in normovolemic surgical patients in comparison with standard care.

**Methods/design:**

SuperAdd is a single-center, prospective, randomized, outcome-assessor blinded, patient blinded controlled trial. The primary outcome is the frequency of postoperative complications identified using the Postoperative Morbidity Survey graded ≥ 2 according to the Clavien-Dindo Score. Adult patients at risk to develop hypalbuminemia, i.e., ASA III or IV or high-risk surgery, are recruited after written informed consent was obtained. The albumin concentration is assessed before the induction of anesthesia and every 3 h until admission to the postanesthesia care unit. If albumin concentrations drop below 30 g/l, patients are randomly allocated to the control or the treatment group. The study intervention is a goal-directed human albumin substitution aimed at a concentration > 30 g/l during surgery and postanesthesia care unit stay. The patients in the control group are treated according to standard clinical care. Postoperative visits are to be performed on days 1, 3, 5, 8, and 15, as well as by telephone 6 months after surgery.

**Discussion:**

SuperAdd is the first clinical trial in a surgical population investigating the effect of a goal-directed albumin substitution aiming at a serum level > 30 g/l. The nonrestrictive selection of patients guarantees that the patients without albumin screening will most likely not develop hypalbuminemia, thus ensuring generalizability of the study results.

**Trial registration:**

EudraCT 2016-001313-24. Registered on 5 September 2016. Clinical Trials NCT03167645. Registered on 18 October 2016 and has the Universal Trial Number (UTN) U1111-1181-2625.

## Background

Postoperative complications contribute significantly to morbidity and mortality. A recent analysis suggests that postoperative mortality is the third leading cause of death, with at least 4.2 million people worldwide dying within 30 days of surgery each year [1]. Accordingly, perioperative research often focuses on prevention and early recognition of postoperative complications. Hypalbuminemia warrants special consideration due to its association with numerous postoperative complications [2–4]. Hypalbuminemia can preexist as a result of a poor preoperative nutritional status, critical or chronic illness, an insufficient hepatic synthesis [5], or can be acquired over the perioperative course due to bleeding or capillary leakage [6].

As an integral component for homeostasis, perioperative hypalbuminemia may promote postoperative complications. Albumin is the major binding and transporting protein of hormones, coagulation factors [7], and drugs. Furthermore, albumin is a key determinant of oncotic pressure in the vascular system [8], which is a prerequisite for organ perfusion [9]. Therefore, it seems reasonable to consider perioperative albumin substitution.

Aside from studies in intensive care patients [10–12], there are only retrospective [13] or small prospective studies in the perioperative setting, with conflicting results [14, 15] and limited significance. These studies were heterogeneous, analyzing different indications, such as treatment of hypovolemia or hypalbuminemia, different regimes of substitution, and different outcome measures. Accordingly, the clinical question as to whether perioperative albumin deficits should be substituted in the perioperative setting cannot be answered based on the published knowledge. We hypothesize that a goal-directed albumin substitution is likely to be beneficial in surgical patients with an acute loss of albumin.

The aim of the SuperAdd trial is to investigate whether substitution of human albumin, aiming to maintain a serum concentration > 30 g/l, is able to reduce postoperative complications in normovolemic surgical patients as compared to standard care.

## Methods

### Study setting

The SuperAdd trial is a single-center, prospective, randomized, outcome-assessor blinded, controlled trial performed in a university hospital (Technical University of Munich, Klinikum rechts der Isar, Germany). The SuperAdd workflow is provided in Fig. 1 and the SPIRIT Checklist as Additional file 1.

**Fig. 1 Fig1:**
[figure not shown]
Schedule of enrolment, interventions, and assessments according to the SPIRIT guidelines [16]. PACU, postanesthesia care unit. The Postoperative Morbidity Survey (POMS) screens nine domains (pulmonary, infectious, cardiovascular, neurological, renal, gastrointestinal, wound, pain, and hematological morbidities) [17]. The severity of the complication is graded according to the Clavien-Dindo Score (Table 1) [18]

### Eligibility criteria

Patients scheduled for surgery in the departments of vascular, abdominal, trauma, or orthopedic surgery are recruited during the preoperative anesthesia visit. Inclusion criteria include: (1) ≥ 18 years old, (2) written informed consent, and (3) being at risk for the development of hypalbuminemia, which was assumed for either (3a) American Society of Anesthesiologists status III or IV or (3b) high-risk surgery such as esophagectomy, liver surgery, pancreatic surgery, open aortic surgery, open leg revascularization, thrombectomy, limb amputation, or revision of knee and hip arthroplasty.

Exclusion criteria are (1) emergency surgery, (2) severe liver cirrhosis (Child-Pugh score C), (3) terminal kidney failure requiring dialysis, (4) patients previously randomized to this trial or participation in another clinical trial in the past three months, in accordance with German medication laws, (5) patients who have a legal guardian for medical decisions, (6) patients with a history of allergy to albumin or auxiliary substances, (7) pregnant women, (8) breastfeeding women, and (9) patients with a body mass index > 35 kg/m^2^.

### Interventions

The study intervention is a goal-directed albumin substitution with boluses of 20 g human albumin given in 100-ml bottles (Human Albumin 20% Behring™, CSL Behring, Marburg, Germany) to reach albumin serum concentrations ≥ 30 g/l throughout surgery and during the postoperative anesthesia care unit (PACU) stay. Albumin solutions will be infused in whole bottles. The number of bottles is related to the difference between the actual and target albumin concentration and the patient’s body weight:
$$ \mathrm{number}\ \mathrm{of}\ \mathrm{albumin}\ \mathrm{bottles}=\left(\mathbf{30}\ \mathbf{g}/\mathbf{l}-\mathrm{albumin}\ \mathrm{concentration}\right)\times \mathrm{bodyweight}\times 4\ \mathrm{l}/{\mathrm{kg}}^2 $$

The effect is controlled and if necessary escalated.

According to standard clinical care, patients of the control group will be not treated with albumin. If hemodynamic instability persists despite normovolemia, exceptions will be allowed, but the target will remain a serum albumin concentration of 20 g/l. The maximum allowed number of albumin bottles is accordingly:
$$ \mathrm{number}\ \mathrm{of}\ \mathrm{albumin}\ \mathrm{bottles}=\left(\mathbf{20}\ \mathbf{g}/\mathbf{l}-\mathrm{albumin}\ \mathrm{concentration}\right)\times \mathrm{bodyweight}\times 4\ \mathrm{l}/{\mathrm{kg}}^2. $$

### Blinding (masking)

The intervention is performed by the unblinded anesthesiologists in the operation room and PACU. Patients remain blinded, and the outcome is assessed by blinded physicians of the corresponding surgical department, assisted by blinded study staff. Neither the albumin concentration nor the infusion is documented on the laboratory report, the anesthesia report, or the PACU report. Statistical analyses as well as the interim analyses are undertaken independently by statisticians blinded to the treatment group allocation.

### Anesthesia and fluid resuscitation

All patients receive anesthesia according to the hospital’s standard procedures for patients with ASA 3 or 4 status or high-risk surgery [19]. In particular, fluid resuscitation guarantees normovolemia using balanced crystalloids and gelatine solutions, in accordance with the German Guidelines for intraoperative fluid substitution [20]. Major bleedings and coagulation disorders are treated according to the German Guidelines for therapy with blood compounds and plasma derivatives [21]. Exceptions include the treatment with fresh frozen plasma and albumin preparations. While albumin is only allowed according to the study protocol, the infusion of fresh frozen plasma is prohibited due to its albumin content, and its usage represents a major protocol violation.

### Outcomes measures

The primary outcome measure is the occurrence and severity of postoperative complications, identified using the Postoperative Morbidity Survey (POMS) assessed on postoperative days 3, 5, 8, and 15 and at hospital discharge, and graded according to the Clavien-Dindo Score. In brief, the POMS counts the number of domains, in which a complication leading to a prolongation of hospitalization occurs. The nine screened domains are pulmonary, infectious, cardiovascular, neurological, renal, gastrointestinal, wound, pain, and hematological morbidities [17]. Since the POMS does not grade the severity of each complication, we additionally grade each complication using the Clavien and Dindo scale (Table 1) [18]. The primary endpoint is the frequency of patients with at least one clinically relevant postoperative complication, graded as Clavien-Dindo Score ≥ 2, on at least one postoperative day until hospital discharge.

**Table 1 Tab1:** Definition of the Clavien-Dindo Score [18]

Grades	Definition
**Grade I**	Any deviation from the normal postoperative course without the need for pharmacological treatment or surgical, endoscopic, and radiological interventions.
	Allowed therapeutic regimens are drugs as antiemetics, antipyretics, analgesics, diuretics, and electrolytes and physiotherapy. This grade also includes wound infections opened at the bedside.
**Grade II**	Requiring pharmacological treatment with drugs other than such allowed for grade I complications. Blood transfusions and total parenteral nutrition are also included.
**Grade III**	Requiring surgical, endoscopic, or radiological intervention.
**Grade III-a**	Intervention not under general anesthesia.
**Grade III-b**	Intervention under general anesthesia.
**Grade IV**	Life-threatening complication (including CNS complications) requiring IC/ICU management.
**Grade IV-a**	Single organ dysfunction (including dialysis).
**Grade IV-b**	Multi-organ dysfunction.
**Grade V**	Death of a patient.

Secondary outcome variables are the subjective quality of recovery, in-hospital and 180-day mortality, length of stay in the PACU, intensive care unit and hospital, incidence of complications and the respective surrogate variables in the nine POMS domains (e.g., acute kidney injury, pulmonary congestion, myocardial injury after noncardiac surgery, perioperative catecholamine requirements, hypotension, infusion, and transfusion), and the efficiency of the albumin substitution.

The quality of recovery is assessed using the Quality of Recovery-9 (QoR-9) Questionnaire preoperatively and postoperatively on days 1, 3, and 180. The QoR-9 Questionnaire is a nine-item scale to determine subjective recovery after surgery (Table 2) in its German version [22, 23]. Total QoR-9 scores range from 0 to 18, with higher scores indicating better recovery.

**Table 2 Tab2:** Quality of Recovery (QoR-9) Questionnaire. Each question can be quoted with 0, 1, or 2 according to the level of agreement. The total score is the sum of all responses. As the last three questions are asked inversely, the scoring scheme is to be inverted

QoR-9 questions	
Had a feeling of general well-being.	
Had support from others (especially doctors and nurses).	
Been able to understand instructions and advice. Not being confused.	
Been able to look after personal toilet and hygiene unaided.	
Been able to pass urine and having no trouble with bowel function.	
Been able to breathe easily.	
Been free from headache, backache, or muscle pains.	
Been free from nausea, dry retching, or vomiting.	
Been free from experiencing severe pain or constant moderate pain.	

Albumin in serum is measured photometrically on a Cobas 8000 c702 analyzer using the original reagent kit (Roche Diagnostics, Mannheim, Germany). High-sensitive cardiac troponin T in serum is measured using a sandwich electrochemiluminescent immunoassay on a Cobas 8000 e602 analyzer and original reagent kits (Roche Diagnostics, Mannheim, Germany). Immature platelets are measured using a fully automated analyzer (Sysmex XE-5000, Sysmex, Kobe, Japan). The device uses two fluorescent dyes containing polymethine and oxazine, which penetrate the cell membrane staining the RNA. Stained cells are then passed through a semiconductor laser beam, allowing differentiation between immature and mature platelets by plotting forward scatter light (measuring cell volume) against fluorescence intensity (representing RNA content) [24].

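### The QoR-9 scoring rule inverts the last three items although Table 2 words them positively, so as printed the total counts freedom from symptoms against the patient

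*Protocol article*

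**What the plan says.** The relevant text is in the protocol article, Methods, Outcomes measures, including the caption and items of Table 2.

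- Item scoring: "Each question can be quoted with 0, 1, or 2 according to the level of agreement".
- Total: "The total score is the sum of all responses".
- Inversion: "As the last three questions are asked inversely, the scoring scheme is to be inverted".
- Range and direction: "Total QoR-9 scores range from 0 to 18, with higher scores indicating better recovery".
- Items 7, 8 and 9 as printed: "Been free from headache, backache, or muscle pains", "Been free from nausea, dry retching, or vomiting" and "Been free from experiencing severe pain or constant moderate pain".
- Language: "The QoR-9 Questionnaire is a nine-item scale to determine subjective recovery after surgery (Table 2) in its German version". The German item wording is not reproduced.

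Subjective quality of recovery is named among the secondary outcomes. It is measured before surgery and on days 1, 3 and 180. The Sub-studies section also plans to use repeated QoR-9 assessments for earlier detection of complications.

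**The concern.** The caption gives a reason for the inversion, namely that the last three questions run in the opposite direction to the others. The printed items do not. Agreeing that one has been free of nausea is a good answer, just as agreeing that one breathes easily is. The agreement scoring, the inversion, the printed wording and the stated direction of the total therefore cannot all be true.

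Anyone who programs the score from this text reverses three of nine items, which carry 6 of the 18 points. Items 7 to 9 cover pain, headache and nausea. With them reversed, a treatment difference in QoR-9 can shrink, vanish or change sign. The sub-study would suffer in the same way, because worsening pain or nausea would raise the score.

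**Working it through.** **Inputs**, all from Outcomes measures and Table 2: nine items; response r_i of 0, 1 or 2, with 2 for full agreement; total is the sum; items 7 to 9 inverted, taken as 2 − r_i; stated range 0 to 18, higher is better.

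Let A be the sum of responses to items 1–6 (0 to 12) and B the sum of responses to items 7–9 (0 to 6). With the printed wording, high A and high B both mean good recovery.

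- Without inversion: T = A + B.
- With the printed rule: T* = A + (6 − B).

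**The plan's own figure.** Enumerating all 3^9 response patterns gives a range of 0 to 18 for both T and T*. The stated range is reproduced either way, so a range check on the data would not detect the problem. The stated direction is not reproduced:

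| Patient (printed item wording) | A | B | T, no inversion | T*, printed rule |
|---|---|---|---|---|
| Full agreement with all nine items | 12 | 6 | 18 | 12 |
| Full disagreement with all nine items | 0 | 0 | 0 | 6 |
| Good on items 1–6, all three symptom groups present | 12 | 0 | 12 | 18 |
| Poor on items 1–6, free of all three symptom groups | 0 | 6 | 6 | 0 |

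Under the printed rule the maximum goes to a patient with all three symptom groups, and the minimum to a patient with none of them. The distance from worst to best recovery falls from 18 − 0 = 18 points to 12 − 6 = 6 points. The error for a single patient is T* − T = 6 − 2B, which runs from +6 (B = 0) to −6 (B = 6).

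**Effect on a group comparison.** Let a and b be the between-group differences in mean A and mean B. The correct difference is a + b; the printed rule gives a − b.

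- Benefit of d on every item: a = 6d, b = 3d. Correct 9d; printed rule 6d − 3d = 3d, one third of the true difference.
- Benefit of d on items 7–9 only: a = 0, b = 3d. Correct +3d; printed rule −3d, so the sign is reversed.
- Benefit of d on items 1–6 only: a = 6d, b = 0. Both give 6d, so no distortion.

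**The other reading.** If the form asks items 7 to 9 negatively (for example, whether the patient had nausea), the best patient answers 2 on items 1–6 and 0 on items 7–9, and scores 12 + 6 = 18. The worst patient answers 0 and 2, and scores 0 + 0 = 0. Range and direction then both agree with the text, and the printed item wording is the mistake.

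**The case against.** The strongest reply is that no score need be wrong. The instrument is used in German, and Table 2 is an English list. The caption makes a factual statement about how the questions are put, and an inversion is normally introduced to achieve exactly the direction the article states. On that view the table prints the concept being scored rather than the question as asked, the inversion is needed, and the effect on the data is zero. It can also be said that the outcome is secondary within an unranked list, and that neither the primary endpoint nor the sample size depends on it.

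Much of this stands. The documents cannot show which side is wrong, the figures of 12 and 6 apply only if the rule is used with the items as printed, and the primary analysis is untouched. The contradiction itself remains, however. On the benign reading Table 2 shows the wrong wording for its own rule, and a programmer or reader who scores from it gets wrong totals. Nor is this a detail that an article leaves to a fuller document, since the article states both the rule and the items, and they conflict.

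**Conclusion.** The concern holds: the scoring rule is wrong as written. With the items in Table 2, full recovery scores 12 instead of 18 and the worst state scores 6 instead of 0. An equal benefit on all items is cut to one third, and a benefit confined to items 7–9 is reversed in sign. These figures assume that patients answer the wording as printed and that inversion means 2 minus the response. If the German form words the three items negatively, the scores are right and the error is confined to the table. An actual scoring error in trial data is therefore possible but not established. The point should be settled because it affects a named patient-reported secondary outcome and a planned sub-study; it does not touch the primary endpoint.

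**What to change.** Compare Table 2 with the German questionnaire actually given to patients, and with the scoring code if it exists.

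- If items 7–9 are worded positively, as printed, delete the inversion.
- If they are worded negatively, keep the inversion and print that wording in Table 2.

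In either case state the scoring of items 7–9 explicitly, for example that 2 points always denote the better state. As a supporting check before database lock, look at whether the scored items 7–9 correlate positively with items 1–6. A clear negative correlation would suggest reversed scoring, but a weak one would settle nothing, so the form remains the deciding evidence.

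The cost is one look at the form and a corrected caption or table. Under Statistical methods no change to the analysis plan is allowed once the database is closed, so the correction must come before then. Trial status describes recruitment as still open, which leaves time.

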### Participant timeline

Patients are screened for eligibility, informed about the study, and asked for their consent during the preoperative anesthesia evaluation by any qualified anesthesiologist on duty. After arrival in the operation theater, albumin assessment starts as the second step of the screening process. For this purpose, albumin concentration is determined before the induction of anesthesia and at least every 3 h until admission to PACU. If the albumin concentration does not drop below 30 g/l, the patient will not be recruited. If the albumin concentration drops below 30 g/l, the patient is to be randomly allocated to the intervention or the control treatment. The randomized patients’ albumin concentration is to be assessed again every 3 h, as well as after each albumin infusion, until the intervention period ends with discharge from the PACU. Postoperative visits are to be performed on days 1, 3, 5, 8, and 15, unless the patient is previously discharged from the hospital. The patient will be contacted via phone 6 months after surgery.

### Recruitment

The stepwise inclusion process is recognized a priori as a bottleneck for recruitment. Therefore, an emphasis was placed in defining a clear sequence of measures and responsibilities. First, we explicitly defined the population to be screened; the patients at surgical risk of losing albumin, specified as a list of high-risk surgical procedures or patients at risk for slow albumin synthesis, specified using the ASA risk score ≥ 3. Accordingly, we trained all anesthesiologists of the department in the correct use of the ASA risk score and the list of high-risk surgical procedures at least every 4 months. Second, we recruit patients of specified surgical departments operating in the same operation theater with 10 operation rooms. The attending anesthesiologists are trained to guarantee sampling of blood according to the given timelines, to ensure their appropriate labeling, to blind the surgical staff, and to prioritize albumin analysis in the department of clinical chemistry. Third, the anesthesiologists are quickly informed about the albumin concentration using telephone- and IT-based information pathways. Finally, the investigational product is prepared to be rapidly delivered by the transfusion department.

### Strategies to improve adherence to intervention protocols

We provide regular lectures for the participating departments. The randomization team can be contacted at any time to assist the anesthesiologists in charge with the requirements of the study protocol, in particular with the intervention. Furthermore, the study protocol is published in our in-house network, which is available on the monitor of the patient data management system. Finally, each anesthesiologist is equipped with a pocket card including major information about the study-related requirements.

### Criteria for discontinuing or modifying allocated interventions

Allergic reactions against the albumin preparation must be reported as a severe adverse event. If this is suspected, the trial medication is to be stopped immediately. Protocol violations, such as infusion of fresh frozen plasma or albumin preparations outside the study intervention, do not lead to termination of participation in the study.

### Sample size

The frequency of complications graded as Clavien-Dindo Score > 2 in surgical patients with preoperative hypalbuminemia has been reported as 52%, compared to 23% in patients with normal albumin concentration, according to an observational study in patients with ovarian cancer [3]. We assumed a clinically relevant treatment effect if albumin substitution could halve the absolute risk difference between patients with hypalbuminemia and normal albumin, i.e., an absolute risk reduction of 14% or a relative risk reduction of approximately 25%. Since a general surgical population was likely to have a different risk of complications related to hypalbuminemia, an interim analysis was planned after 100 patients, so as to better estimate the risk of complications in the study population and recalculate the sample size using a 25% relative risk reduction.

After inclusion of 100 patients, an independent statistician compared the two treatment groups for the incidence of any postoperative complications graded as Clavien-Dindo ≥2 and > 2, using a two-sided *χ*^2^ test for independent samples. Had the difference between groups reached a significance level of 0.002, the study would have been terminated. Since the incidences of complications graded as Clavien-Dindo ≥ 2 after 100 patients were 82% vs. 84% (*p* = 0.79) and those scored Clavien-Dindo > 2 were 34% vs. 36% (*p* = 0.83), the study must be continued. Hence, the 95% confidence interval of the relative risk for complications graded Clavien-Dindo ≥ 2 includes the postulated 25% relative risk reduction (0.87 [0.37–2.03]), the interim analysis also failed to show a missing treatment effect, which would also terminate the study. Based on incidences of the interim analysis, a significance level of 0.048, and a power of 80%, a sample size of 4408 patients would be required to prove significance. In fact, the study was limited to 300 patients per group, according to the prerequisite given by the responsible authority, the Paul-Ehrlich-Institut. Based on the limited number of 2 × 300 patients, the frequencies of complication of 82% and 84% and a significance level of 0.048, the power would be 50%.

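### The reported recalculation and power rest on the observed interim difference (82% vs 84%), not on the planned 25% relative risk reduction, which was itself never justified for the primary endpoint

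*Protocol article*

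**What the plan says.** All of this stands in the protocol article. Under Sample size, the target effect starts from an observational study in ovarian cancer: "The frequency of complications graded as Clavien-Dindo Score > 2 in surgical patients with preoperative hypalbuminemia has been reported as 52%, compared to 23" per cent, the second figure being for normal albumin. Halving that gap is presented as an absolute reduction of 14 points or a relative reduction of about 25%. Because a general surgical population might carry a different risk, an interim analysis after 100 patients was planned to "better estimate the risk of complications in the study population and recalculate the sample size using a 25% relative risk reduction".

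The next paragraph gives the interim rates. Complications "graded as Clavien-Dindo ≥ 2 after 100 patients were 82% vs. 84" per cent, and "those scored Clavien-Dindo > 2 were 34% vs. 36" per cent. The recalculation follows and names the number needed: "Based on incidences of the interim analysis, a significance level of 0.048, and a power of 80%, a sample size of 4408 patients". Power for the capped size of 300 per group is then given as 50%, from the same two rates, 82% and 84%.

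Under Outcomes measures the endpoint is set at the lower threshold: "The primary endpoint is the frequency of patients with at least one clinically relevant postoperative complication, graded as Clavien-Dindo Score ≥ 2". Statistical methods repeats this and specifies a two-sided chi-square test. The Discussion says the interim differences were so small that about 9000 patients would be needed.

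**The concern.** The stated rule updates the complication risk from the interim data and holds the effect fixed at 25% relative. The reported calculation replaces the effect as well, with a difference observed in 100 patients. That answers another question: how large a trial would have to be if the interim difference happened to be the truth. Neither a sample size nor a power for the 25% reduction is given.

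The second problem is where the 25% comes from. It was derived at a 52% risk of complications graded > 2, while the primary endpoint counts grade 2 as well and has a risk above 80%. The interim rates show how far apart the two thresholds lie (82/84% against 34/36%).

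The stake is interpretation. The Discussion says that no benefit in 600 patients would settle the matter against substitution on grounds of cost. That inference needs known power against a stated relevant effect, and the only power printed is for a 2-point effect that was never called relevant.

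**Working it through.** **Inputs.** From Sample size: interim rates 82% and 84% (≥ 2) and 34% and 36% (> 2), alpha 0.048, 80% power, 300 per group, target 25% relative. From Statistical methods: two-sided test. From Allocation: 1:1. Two assumptions are mine. The higher rate is taken as control, since the text does not label the groups. The interim groups are taken as 50 each, which reproduces both printed p-values (0.79 and 0.83).

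**Formula.** Per group, n = [z_a·√(2·p̄(1−p̄)) + z_b·√(p1(1−p1) + p2(1−p2))]² / (p1−p2)², with p̄ the mean of the two rates, z_a = 1.977 (two-sided 0.048) and z_b = 0.842. Power is obtained by solving the same expression for z_b at n = 300.

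**1. The article's own figure.** For 84% vs 82%:
- Two-sided: (1.0504 + 0.4469)² / 0.02² gives 5,606 per group, 11,212 in total.
- One-sided (z = 1.665): (0.8843 + 0.4469)² / 0.02² gives 4,431 per group, 8,862 in total.

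The printed 4408 is thus close to a one-sided number per group, which also fits the 9000 in the Discussion. It does not fit the planned two-sided test, and it does not reproduce as a total. This confirms that the observed difference was the input: 0.02/0.84 = 2.4% relative.

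**2. The printed power.** For 84% vs 82% at 300 per group, power is about 9 to 10% two-sided and about 16% one-sided. Neither is 50%.

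**3. How firm the substituted effect is.** With 50 per group the standard error is √(0.84·0.16/50 + 0.82·0.18/50) = 0.0751. The interval is 0.02 ± 1.96·0.0751 = 0.02 ± 0.147, or about -13 to +17 points.

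**4. The planned rule on the primary endpoint.** 84% × 0.75 = 63%, a 21-point reduction. (1.2342 + 0.5102)² / 0.21² gives 69 per group, 138 in total. Power at 300 per group exceeds 99.9%. With 82% as the control rate (to 61.5%) it is 76 per group, 152 in total.

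**5. The same 25% on the endpoint it was derived for.** 36% × 0.75 = 27%. (1.2990 + 0.5503)² / 0.09² gives 423 per group, 846 in total. Power at 300 per group is about 65%.

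**6. What 300 per group can detect.** From 84%, 80% power is reached at about 74.7%: 9.3 points, or about 11% relative.

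**7. The planned effect against the interim data.** With 41/50 vs 42/50 the relative risk is 0.82/0.84 = 0.98. The standard error of its logarithm is √(1/41 − 1/50 + 1/42 − 1/50) = 0.0906, so the 95% interval is 0.82 to 1.17, which excludes 0.75. The article prints 0.87 (0.37–2.03) as the relative risk. The value 0.87 is the odds ratio, (41×8)/(42×9) = 0.868, and the printed interval matches neither measure under this assumption (odds ratio: 0.31 to 2.47).

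**The case against.** The strongest reply is that nothing in the conduct of the trial turns on this. The authority limited the trial to 300 per group beforehand, so 4408 set nothing. That stands. A reader might infer that the wrong calculation gave the trial its size; the article does not support that.

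The Discussion also calls the sample size calculation a major limitation, gives the interim a second purpose (a first view of the treatment difference), and says how a null result at 600 will be read. So it would go too far to say that the final result has nothing to be judged against. These statements still do not explain why the 25% rule was dropped.

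A reader might also infer that 14 points and 25% are contradictory targets, because at 84% they part (14/84 is about 17%). That is arithmetic at a new baseline. The article expected a different risk and named the relative scale for the recalculation. What remains is narrower: 25% was not justified for the ≥ 2 endpoint.

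Finally, power above 99.9% could be read as proof that the trial is amply powered. It is not, because with 50 per group that effect already lies outside the interim interval.

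**Conclusion.** The point holds as a reporting error with consequences for interpretation. The reported sample size and power depart from the rule stated in the same section, and the 25% in that rule was carried over from a different severity threshold without justification. By the planned rule the requirement is 138 to 152 patients in total, and the cap gives more than 99.9% power. The effect in question is a 21-point reduction that the interim relative risk of 0.98 (0.82–1.17) already excludes. The more useful statement for reading the final result is the detectable difference of about 9.3 points, which lies inside the interim interval of -13 to +17.

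The figures that were printed are also wrong on their own inputs: about 11,212 patients in total and 9 to 10% power for a two-sided test, against 4408 and 50%.

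The sample sizes and powers rest on the pooled two-proportion formula, 1:1 allocation and 84% as the control risk; the interim intervals rest on the assumed 50 per group. The correction should be made, but it does not touch enrolment.

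**What to change.** Leave the 600-patient cap as it is and revise the Sample size text and the matching Discussion sentences before the database is closed:

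- Report the recalculation by the planned rule on the ≥ 2 endpoint: 84% to 63%, two-sided alpha 0.048, 80% power, about 69 per group (138 in total), with more than 99.9% power at 300 per group.
- State the difference detectable with 80% power at 300 per group: about 84% vs 74.7%, 9.3 points, about 11% relative.
- Say that the 25% was derived for complications graded > 2, where 36% to 27% would need about 423 per group and has about 65% power at 300 per group. Either justify 25% for ≥ 2 or say that it was not justified.
- Flag any other target, such as 14 points, as chosen after the interim rates were known.
- Mark figures from 82% vs 84% as descriptive and correct them to about 5,606 per group (11,212 in total) and about 9 to 10% power.
- Give the actual interim group sizes and the relative risk with its interval (about 0.98, 0.82–1.17, if 50 per group), and note that it excludes a 25% reduction.

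The cost is recomputed text; recruitment, treatment and the primary test are unaffected.
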